##### Thirty-day mortality

This is defined as death during the first 30 days after the operation from causes related or unrelated to TIVAP implantation. In the event of not being able to talk to the patient at the 30-day telephone interview, the study nurse will contact the relatives or family physician to ask them whether the patient has died, and if so, the cause of death.

##### Thirty-day morbidity

This is defined as the occurrence of any of the complications listed in Table 1, known as possible peri- and post-operative complications of TIVAP implantation leading to deviation from the expected post-operative course. Peri- and post-operative complications of port implantation will be recorded with tick boxes in the CRF on the day of operation and at visit three (30 days after operation, by telephone questionnaire) by the surgeon and/or study nurses. All complications will be rated according to the Clavien-Dindo classification of surgical complications (Table 2) [20]. In the event of not being able to talk to the patient at the 30-day telephone interview, the study nurse will contact the relatives or family physician to ask them for information regarding the follow-up criteria.

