**Table 1 Tab1:** **Definitions of peri- and post-operative complications**

**Complication**	**Definition**
Intra-operative lesion of nerves	Clinical diagnosis and/or EMG findings
Dislocation of the catheter and/or the port chamber	Radiological finding
Incompatibility of contrast agent	Any allergic reaction against a contrast agent needing medical treatment with drugs
Thrombosis	Sonographic findings and/or phlebography
Post-operative bleeding	Clinical diagnosis during reoperation
Haematoma	Clinical diagnosis, no reoperation necessary
Disconnection or breakage of the catheter	Radiological findings, findings after explantation
Extravasation of injected fluid	Radiological findings and/or clinical diagnosis
Wound infection	Clinical diagnosis, wound has to be reopened and/or antibiotic treatment
Catheter sepsis	Two or more of the following symptoms:
	Temperature over 38.3°C or under 36°C;
	Heart rate over 90 beats per minute;
	Respiration rate over 20 breaths per minute, PaCO_2_ < 32 mmHg (spontaneous breathing) or PaO_2_/FiO_2_ < 200 mmHg (mechanical ventilation);
	Total peripheral WBC count >12 G/L or WBC <4.0 G/L or >10% immature neutrophils (bands), regardless of total peripheral WBC count;
	Plasma C-reactive protein >2 SD above normal value and positive findings in bacteriology of the port catheter pike
Cutaneous necrosis	Clinical diagnosis and/or histological finding
Pinch-off phenomenon	Radiological findings and/or clinical diagnosis

EMG: electromyography; PaCO2: partial pressure of carbon dioxide; PaO2: partial pressure of oxygen; FiO2: fraction of inspiratory oxygen; mmHg: millimetres of mercury; WBC: white blood cells.

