#### Study-specific serious adverse events

As it can be anticipated that many events fulfilling the SAE criteria will be caused by the underlying disease or treatment and will not be related to trial intervention (for example, hospitalisation due to neutropenic fever after CHT), only SAEs not related to the underlying disease or treatment will have to be reported. Anticipated SAEs due to the underlying disease that do not have to be reported include the following:hospitalisation due to progress of underlying disease;hospitalisation due to bone marrow toxicity of CHT, including:neutropenic fever,anaemia requiring transfusion of red blood cell concentrates,haemorrhagic events necessitating intervention/transfusion due to thrombocytopenia;hospitalisation due to severe nausea, vomiting and exsiccosis caused by CHT;hospitalisation due to severe impairment of hepatic/renal function related to CHT.

The occurrence of pneumothorax and haemothorax will be documented as SAEs for safety reasons.

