## Discussion

TIVAP implantation is one of the most common general surgical procedures [3] and is performed routinely by either SCD or PSV. However, only few randomised controlled trials [4,6,9,17] and no multicentre trials compared these techniques for their potential risks and benefits. The aim of the PORTAS-3 trial is to compare a primary open strategy (SCD with RT if necessary; PSV if the aforementioned fail) to a primary closed strategy (PSV; SCD if PSV fails) in regard to the frequency of post-operative pneumothorax and haemothorax, with the hypothesis that the open strategy is able to significantly reduce the risk of pneumothorax and haemothorax occurrence.

The PORTAS-3 trial is designed as a pragmatic trial, since the objective is to depict the real medical treatment situation. Therefore, just some key steps of the interventions are predefined, and the rest can be performed according to local practice of the centres. For instance, in PSV either sonography, fluoroscopy or anatomical landmarks can be used for guidance of the puncture. Some authors suggested that sonographic guidance should be the method of choice for vascular cannulation due to improved safety [26]. Even though ultrasound is widely available nowadays, this still does not represent comprehensive clinical practice in a lot of hospitals, and a recent Cochrane review on ultrasound guidance for subclavian vein catheterization [27] could only show a reduced risk of arterial cannulation, and no reduction for other complications like pneumothorax and haemothorax.

The results of the PORTAS-3 trial will be applicable to a wide range of patients and could influence future guidelines and decision-making. Healthcare costs might be reduced by the reduction of complications and necessary treatment and hospitalization for these complications. Furthermore, required treatment of patients (for example, with CHT) will not be delayed by potential complications.

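### Thirty-day morbidity is limited to Table 1, which omits pneumothorax and haemothorax, so it is not overall morbidity; and the catheter-sepsis row as printed can be met without a positive culture

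*Protocol article*

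**What the plan says.** Under Secondary endpoints, Thirty-day morbidity, the protocol article states: "This is defined as the occurrence of any of the complications listed in Table 1". The same paragraph introduces the listed events as known possible complications of port implantation and says that all complications will be graded by Clavien-Dindo. No other endpoint paragraph mentions that grading.

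Table 1 has 12 rows. Pneumothorax and haemothorax are not among them. The Background names three risks specific to subclavian puncture: pinch-off, pneumothorax and haemothorax. Only pinch-off has a row.

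The catheter-sepsis row opens with "Two or more of the following symptoms". The items that follow include "Temperature over 38.3°C or under 36°C" and "Total peripheral WBC count >12 G/L or WBC <4.0 G/L". The last item reads "Plasma C-reactive protein >2 SD above normal value and positive findings in bacteriology of the port catheter pike". Bacteriology appears nowhere else in the row.

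Under Study-specific serious adverse events, the events that need not be reported include "hospitalisation due to bone marrow toxicity of CHT", with neutropenic fever given as an example. The same section requires pneumothorax and haemothorax to be documented as SAEs. Under Further analyses, secondary variables are analysed descriptively, with descriptive P values and 95% confidence intervals.

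**The concern.** There are two separate problems with one endpoint.

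The first is its content. The trial describes itself as a comparison of complication rates, and a between-arm figure labelled 30-day morbidity will be read as the overall complication burden of each strategy. It leaves out the two events that the trial was designed to study, which are expected mainly after puncture. The article does not say that this separation is intended. Because grading is specified only in the morbidity paragraph, it is also unclear whether these events receive a Clavien-Dindo grade, although the Background says that most need further treatment and often hospital admission.

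The second is the sepsis definition. All patients have an oncological disease, and the protocol itself anticipates neutropenic fever after chemotherapy. A rule that accepts any two systemic signs without proof of port infection would record some of that fever as catheter sepsis. One episode could then be a port complication in the morbidity table and a non-reportable chemotherapy effect in the safety data.

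**Working it through.** **Inputs, all from the Sample size section:** event rate 3% (closed) and about 0.5% (open, from 0.175 × 0.03 = 0.525%); 577 patients per group; power 0.9; type 1 error 0.05 (two-sided according to the section on testing the primary hypothesis); no missing values.

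**1. The plan's own figure.** For a two-sided chi-square test without continuity correction, with mean rate 0.0175:

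n = [1.960 × √(2 × 0.0175 × 0.9825) + 1.282 × √(0.03 × 0.97 + 0.005 × 0.995)]² / 0.025² ≈ 576.04, rounded up to 577.

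This reproduces the stated 577 per group (1,154 in total). It depends only on the primary endpoint, so nothing below changes it.

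**2. Primary events outside the morbidity count.**
- Closed: 577 × 0.03 = 17.3 patients.
- Open: 577 × 0.005 = 2.9 patients (3.0 with the unrounded 0.525%).
- Gap: 17.3 − 2.9 = 14.4 patients, and 14.4 / 577 = 2.5 points.

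These are upper limits. A patient who also has a Table 1 complication is counted anyway.

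**3. Effect on the morbidity comparison.** Assume that Table 1 complications occur at the same rate b in both arms, independently of pneumothorax and haemothorax. The document gives no such rate, so b is varied. The Table 1 difference is then 0. With the primary events included, morbidity in an arm is 1 − (1 − b)(1 − p), and the closed-minus-open difference is (1 − b) × 0.025.

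| b (assumed) | Closed | Open | Difference |
|---|---|---|---|
| 5% | 7.9% | 5.5% | 2.4 points |
| 10% | 12.7% | 10.5% | 2.3 points |
| 15% | 17.6% | 15.4% | 2.1 points |

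So the omission hides about 2.1 to 2.4 points under these assumptions, and at most 2.5.

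**4. The sepsis row, read as printed.** The items are separated by semicolons. Temperature above 38.3°C satisfies one and a white count below 4.0 G/L satisfies another. That makes two, and neither refers to bacteriology. The culture result is joined only to C-reactive protein, so it is needed only when that item is used as one of the two.

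**5. Direction of the resulting error.** Chemotherapy-related fever should be about equally frequent in randomised arms. As an illustration only, assume true morbidity of 10% (closed) and 7.5% (open), and a false-sepsis rate f that is equal in both arms and independent of true morbidity. Observed morbidity is 1 − (1 − true)(1 − f).

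| f (assumed) | Closed | Open | Risk difference | Risk ratio |
|---|---|---|---|---|
| 0 | 10.0% | 7.5% | 2.50 points | 0.75 |
| 2% | 11.8% | 9.35% | 2.45 points | 0.79 |
| 5% | 14.5% | 12.1% | 2.4 points | 0.84 |
| 10% | 19.0% | 16.75% | 2.25 points | 0.88 |

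The effect is attenuation towards no difference, more visible on the ratio than on the difference scale.

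**The case against.** The strongest reply is that nothing is lost. Pneumothorax and haemothorax have their own definition, radiographic assessment after puncture and day-30 inquiry. They are the confirmatory comparison and are also recorded as SAEs. Keeping the primary endpoint out of a secondary one is a defensible choice, and the 2.5 points are the very difference that the trial reports first. This stands, and it rules out reading the omission as lost safety data. What remains is that the separation is unstated, the label suggests more than the list delivers, and grading of these events is not clearly provided for.

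A reader might infer that Table 1 ignores the harms of puncture altogether. It does not: pinch-off has a row, and so does contrast-agent incompatibility, which is relevant to fluoroscopy-guided puncture. A reader might also count the absence of kinking and arterial puncture as bias between the arms. The Background says that kinking is seen with both techniques. Arterial cannulation appears only in a Discussion remark that a review "could only show a reduced risk of arterial cannulation", with no rate, and consequences such as haematoma or bleeding are in Table 1.

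On sepsis, the closing words can be read as a condition on the whole row, since a culture result is not a symptom, and the layout of a machine-read table cannot settle the matter. That reading is possible, but the punctuation as printed supports the other one, and the two give different endpoints. It can also be said that an endpoint definition and an SAE exemption serve different purposes. That is fair as far as the rules go, but attributing the same episode to the port in one place and to chemotherapy in the other is still inconsistent.

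**Conclusion.** The concern holds in a limited form. Thirty-day morbidity as defined is morbidity other than pneumothorax and haemothorax. Taken as overall morbidity, it leaves out up to about 17 closed-arm and 3 open-arm patients and looks up to about 2.5 points too favourable to the closed strategy. This rests on the plan's 3% and 0.5%, on 577 patients per arm, and on no overlap with Table 1 complications. With assumed background rates of 5 to 15%, the shift is 2.1 to 2.4 points.

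The catheter-sepsis row, followed as printed, admits fever with leukopenia without a culture and so would misclassify chemotherapy-related neutropenic fever. A reader might infer that this favours one arm or inflates the sepsis count by a known number. The documents support neither: randomisation should balance such episodes, so the comparison is diluted, and no neutropenic-fever rate is given from which a count could be derived.

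The endpoint is secondary and descriptive. The primary test, the sample size and the confirmatory conclusion are untouched.

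**What to change.** 1. Report 30-day morbidity twice: Table 1 complications alone, and Table 1 complications plus pneumothorax and haemothorax. State that the first excludes the primary-endpoint events.
2. State that pneumothorax and haemothorax are also graded by Clavien-Dindo.
3. Reword catheter sepsis as two or more systemic criteria AND, as a separate condition that always applies, positive port or catheter bacteriology.
4. Optionally, add arterial puncture and kinking to Table 1.

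Items 1 and 2 use events that are already collected and cost a little extra tabulation and grading. Item 3 changes one definition in the case report form. Since recruitment began in November 2014, sepsis entries already recorded need to be re-checked against the culture result. Item 4 would need back-entry from operation records for patients already treated.

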### Primary and secondary endpoints

#### Primary endpoint

The primary endpoint will be the frequency of post-interventional pneumothorax and haemothorax. Pneumothorax and haemothorax will be defined as the presence of air or blood in the pleural space, respectively. The rate of pneumothorax and haemothorax will be assessed two hours post-implantation by means of a chest X-ray (in inspiration) by the responsible physician if PSV was performed. In the event that SCD with or without RT is successful, a chest X-ray will be performed only in patients with suspicion or symptoms of pneumothorax or haemothorax (for example dyspnoea), since SCD has no associated risk of these conditions. A copy of the post-operative pneumothorax and/or haemothorax control radiograph will be saved in digital form, using radiological image viewing software (such as Centricity®, GE Healthcare, Buckinghamshire, United Kingdom), or a copy of the original radiograph will be archived. The presence of pneumothorax and haemothorax will be documented in the case report form (CRF). At follow-up visit three on day 30, the study nurse will also ask the patient about further post-operative occurrence of pneumothorax and haemothorax and check the patient’s documents for further diagnostic and treatment procedures in this regard.

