#### Visit three

Patients will be called by a study nurse on day 30 post-operation and asked about SAE and primary and secondary endpoints by means of a standardised questionnaire. All data will be documented in the CRF.

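### Day-30 morbidity rests on a telephone report with no stated records check, although about five of the twelve Table 1 complications are defined by imaging, reoperation, explantation or laboratory findings

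*Protocol article*

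**What the plan says.** The section Thirty-day morbidity gives the definition: "This is defined as the occurrence of any of the complications listed in Table 1". Complications are recorded with tick boxes on the operation day and again "at visit three (30 days after operation, by telephone questionnaire) by the surgeon and/or study nurses". The section Visit three describes the contact: "Patients will be called by a study nurse on day 30 post-operation and asked about SAE and primary and secondary endpoints", using a standardised questionnaire. If the patient cannot be spoken to, "the study nurse will contact the relatives or family physician to ask them for information regarding the follow-up criteria". Table 3 lists no post-operative contact other than this one.

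Table 1 sets the criterion for each complication. Thrombosis is defined by "Sonographic findings and/or phlebography", and post-operative bleeding by "Clinical diagnosis during reoperation".

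The section Primary endpoint adds a further step at the same day-30 visit, in which the nurse is to "check the patient’s documents for further diagnostic and treatment procedures in this regard". In context the last three words of that quote refer to pneumothorax and haemothorax. No corresponding step is stated for the Table 1 complications.

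**The concern.** The endpoint is defined by one kind of evidence and collected, after the operation day, through another. Some Table 1 definitions turn on a radiograph, a phlebogram, an operative finding or a laboratory value. The stated source is what a patient says by telephone a month later, or what a relative or family physician says in the patient's place.

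Two things could follow. An event that meets its definition may be forgotten or not understood, and so lost. An event that does not meet its definition may be reported in good faith and ticked. Patients and surgeons know the allocation, and the section on minimising measurement bias defends only the primary endpoint as objectively assessable. The two kinds of error therefore need not be equal in the two arms.

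At stake are the published 30-day morbidity rates and the between-group comparison. The section Further analyses promises descriptive P values and 95% confidence intervals for secondary variables.

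**Working it through.** No stated figure bears on this point. The article's sample size of 577 per group concerns the primary endpoint. It reproduces from 3% versus 0.5%, two-sided 5% and 90% power with an uncorrected chi-square test: (1.960·√(2·0.0175·0.9825) + 1.282·√(0.03·0.97 + 0.005·0.995))² / 0.025² ≈ 576.04, rounded up to 577. It says nothing about morbidity, so the check is a comparison of definition with source.

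**Step 1. Sort the twelve rows of Table 1 by the evidence they require.**

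| Evidence required | Rows | Count |
|---|---|---|
| Imaging, reoperation, explantation, or measured clinical and laboratory values | Dislocation; thrombosis; post-operative bleeding; disconnection or breakage; catheter sepsis | 5 |
| A clinical diagnosis suffices, or suffices together with treatment given | Nerve lesion; haematoma; extravasation; wound infection; cutaneous necrosis; pinch-off | 6 |
| A treated reaction, with no diagnostic finding named | Contrast agent incompatibility | 1 |

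The total is 5 + 6 + 1 = 12. The count of five is approximate. Catheter sepsis mixes vital signs with blood-gas, white-cell, C-reactive protein and bacteriology criteria, and the layout leaves open whether bacteriology is always needed. On either reading it needs measured values.

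**Step 2. Set the day-30 sources side by side.**

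| Outcome | Telephone call | Document check stated | SAE form |
|---|---|---|---|
| Pneumothorax, haemothorax | Yes | Yes | Yes, always |
| Table 1 event meeting an SAE criterion | Yes | No | Yes, unless attributed to the disease or its treatment |
| Table 1 event not meeting an SAE criterion | Yes | No | No |

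The last row is the gap. A thrombosis found and treated as an outpatient is an example.

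**Step 3. Direction of the error.** Let p be the true rate in an arm, and Se and Sp the sensitivity and specificity of the day-30 record. The observed rate is Se·p + (1 − Sp)·(1 − p). If Se and Sp are the same in both arms, the observed difference is (Se + Sp − 1) times the true difference, which shrinks it. If they differ between arms, as is possible without blinding, the observed difference can be too small or too large. The document gives no p, Se or Sp for morbidity, so neither direction nor size can be settled.

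**The case against.** The strongest reply is that a definition and a method of collection are different things. Table 1 says what makes an event a thrombosis, and the call asks whether one was diagnosed. A patient can relay an ultrasound result, a reoperation or an explantation. This stands. A reader might infer that the visit-three part cannot be scored as defined, or that this applies to every complication. The document does not support that. Seven of the twelve rows accept a clinical diagnosis or a treated reaction, a diagnosis already made can be reported, the family physician is a fallback source, and the surgeon may be the one who records. Nor does anything in the text tell staff to tick a diagnosis on the strength of a symptom.

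The SAE route also counts. Under Safety aspects, investigators assess SAEs up to day 30 from surgical findings and clinical course, so many bleeds needing reoperation and septic admissions should reach a form. It is only a partial remedy. It omits non-serious events, it exempts those attributed to the disease or its treatment (hospitalisation for neutropenic fever is listed), and the article does not say that SAE forms feed the morbidity boxes.

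Two further inferences go too far. One is that the Clavien-Dindo grade has no source: Table 2 grades mostly by treatment received, which patients and physicians can often report. The other is a stated loss of power. Any such figure needs assumed morbidity rates and error rates, and no power is claimed for this endpoint. The document also does not say what share of these complications arises after the operation day.

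Finally, the article is condensed, and the questionnaire, case report form and monitoring manual are not shown. Source verification may be set out there. That tempers the point but does not remove it, because the article itself states a document check for one outcome and a telephone questionnaire alone for the other.

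**Conclusion.** The point holds as an ascertainment weakness. For about five of the twelve Table 1 items, occurrences after discharge that are not serious depend on unverified report in an unblinded trial and may be misclassified in either direction. All 1,154 planned patients pass through this visit, but the number of events affected cannot be derived from the document.

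The consequence is limited. Morbidity is a secondary endpoint, analysed descriptively and collected the same way in both arms, and the primary endpoint is untouched. The conclusion assumes that the day-30 document check means what it says, namely pneumothorax and haemothorax only, and that no unshown document extends it. The change is worth making because it is cheap and would let the reported rates match their own definitions.

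**What to change.** In the sections Thirty-day morbidity and Visit three:

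- Extend the day-30 document check already described under Primary endpoint to every Table 1 complication, and have the SAE forms consulted at the same time.
- Mark each event reported at visit three either as confirmed against its Table 1 definition or as reported but unconfirmed.
- Tabulate 30-day morbidity by arm twice, once for confirmed events and once for all reported events, so that readers can see how far the result depends on unverified report.

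The cost is some extra nurse time, although the nurse already opens the patient's documents at this visit, and one additional case report form field per complication. Where outside records cannot be obtained, some events will stay unconfirmed, and the two tabulations make that visible.
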